### Eligibility criteria

Inclusion criteria
^
6
^ will be as follows:
•Children aged three to seven years old who are healthy and free of any systemic disease•Deciduous teeth indicated for crowns•Deciduous teeth having two-thirds of root structure left radiographically•Presence of one-third of crown shape

Exclusion criteria
^
6
^
•A pathological discrepancy of root resorption•Inflammation at the furcation area•The child having oral parafunctional habits•Deciduous teeth having not sufficient crown structure•Teeth with root caries

Evaluation criteria

The study will be clinically evaluated from the following criteria: crown retention, modified gingival index, plaque index, stain resistance, gingival marginal extension, occlusion, proximal contact, opposing tooth wear, and radiographic assessment.

Clinician’s Satisfaction Criteria will be as follows: surface gloss, roughness, stain resistance, aesthetic, anatomical form, crown fracture, recurrent caries. Parental satisfaction ratings of aesthetic characteristics and their impact of treatment on their children will be evaluated on the basis of size, shape, color and stain using five-point Likert’s scale.

### Sample size

A sample size of children aged three- to seven-years-old will be selected and 72 primary teeth requiring crowns will be randomly distributed in three groups of 24, as follows:

$$N=\frac{{\left(Z_{\left(\alpha /2\right)}+Z_{\beta }\right)}^{2}\left(P_{1}\left(1-P_{1}\right)+P_{2}\left(1-P_{2}\right)\right)}{{\left(P_{2}-P_{1}\right)}^{2}}$$
(1)

$$Z_{\alpha /2}=\text{at 99\% (CI)}=2.576$$

Represents the desired level of statistical significance

$Z_{\beta }=1.28$
: Represents the desired power = 1.28 for 90%

*N* = Minimum samples required for each group

Where,

*P*
_1_ = Estimated proportion of study outcome (Child satisfaction % Experimental group) = 99.99% (Approximate to 100%)
(1)
^
1
^

*P*
_2_ = Estimated proportion of study outcome (Child satisfaction % Control group) = 53.33%
^
1
^

At a level of significance at 1% and power 90%

The minimum sample size required:

$$N={\left(2.576+1.28\right)}^{2}\;{\left(0.999\right)}^{*}\;\left(1-0.999\right)+{\left(0.533\right)}^{*}\;\left(1-0.533\right)/0.466=22\;\mathrm{per}\;\text{group}$$

Considering 10% dropout=2

Samples required22+2=24each

$$\text{Total samples required for three groups}=3^{*}N=72\;\text{total}$$

Mathew
*et al.,* showed the difference between the two proportions of child satisfaction (%) as the primary variable
(1)
^
1
^

P1(for the experimental group) = 100% (considered as 99.999% approx to 100%) and for the control group (53.333%). We considered a clinically significant margin of difference at 46.666%. Also, we considered the assumption for statistical significance, the highest statistical significance level of 1% alpha value with power (1-beta) at 90%.

We use the test statistics of two independent proportion sample size calculations with the given formula samples for taking the minimum samples required in each group.

Calculated with 22 samples required in each group, adding 10% of dropout = 2. A total of 22 + 2 = 24 samples are required in each group, with a sample size of 72 children distributed in three groups.

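### The stated 22 per group does not follow from the printed formula, which gives about 17.1 (18 per group), and adding 2 for 10% dropout falls slightly short of that minimum.

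*Protocol article*

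**What the plan says.** All of this stands in the protocol article, Methods, Sample size.

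- **Formula (1)** is the unpooled-variance formula for two independent proportions, with the squared difference in the denominator. The text names it as the source of the result: "We use the test statistics of two independent proportion sample size calculations with the given formula".
- **Error rates.** The level is 1% and the power 90% ("At a level of significance at 1% and power 90" per cent). The two-sided normal quantile is 2.576, and 1.28 is used for power.
- **Proportions.** Experimental arm: "Estimated proportion of study outcome (Child satisfaction % Experimental group) = 99.99% (Approximate to 100" per cent. Control arm: "Estimated proportion of study outcome (Child satisfaction % Control group) = 53.33" per cent. The experimental proportion also appears as 0.999 in the worked line and as 99.999% and 100% in the closing text.
- **Difference.** "We considered a clinically significant margin of difference at 46.666" per cent, entered in the worked line as 0.466.
- **Result.** The worked line ends in a division by 0.466, not squared, and gives 22 per group. Then: "Calculated with 22 samples required in each group, adding 10% of dropout = 2". That makes 24 per group and 72 over three groups.

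**The concern.** This is the article's only justification for 72 teeth, and its three parts disagree. The formula, the substitution and the answer are three different numbers. A reader who follows the text cannot reproduce 22 and cannot tell which method was used.

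The dropout step raises a second, smaller question. Adding 10% of 22 is not the same as enrolling enough that 22 remain after 10% are lost. If 22 is the minimum, as the section defines N, the allowance should cover the loss that it names.

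What is at stake is whether the stated power rests on a calculation that can be checked, and whether it still holds after the planned attrition.

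**Working it through.** **Inputs, all from the Sample size section.** Zα/2 = 2.576; Zβ = 1.28; P1 = 0.999 and P2 = 0.533 (worked line), or 0.9999 and 0.5333 (definitions), or 0.99999 and 0.53333 (closing text, rounded); difference 0.466 in the worked line; dropout 10%.

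**1. Formula (1) as printed**, N = (Zα/2 + Zβ)² × [P1(1−P1) + P2(1−P2)] / (P2−P1)².

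- (2.576 + 1.28)² = 14.869
- 0.999 × 0.001 + 0.533 × 0.467 = 0.24991
- 0.466² = 0.21716
- N = 14.869 × 0.24991 / 0.21716 = 17.11, so 18 per group

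With 0.9999 and 0.5333 it gives 17.00 (17.005 before rounding). With 0.99999 and 0.53333 it gives 16.99. No printed version of P1 leads to 22.

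**2. The worked line.** With the brackets of formula (1) restored but the denominator left unsquared: 14.869 × 0.24991 / 0.466 = 7.97. Restoring the square as well returns 17.11.

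**3. What does give 22.**

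- *Pooled variance*: N = [Zα/2 √(2p̄(1−p̄)) + Zβ √(P1(1−P1) + P2(1−P2))]² / (P2−P1)², with p̄ = (0.999 + 0.533)/2 = 0.766. This is [2.576 × 0.59874 + 1.28 × 0.49991]² / 0.21716 = 21.93, so 22. The other printed values of P1 and P2 give 21.8.
- *Printed formula with continuity correction*: N' = (N/4) × [1 + √(1 + 4/(N × |P2−P1|))]². With N = 17.11 and 0.466 it gives 21.19, so 22. The other printed values give 21.1.

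Both round up to 22, so the article's number is reachable from its inputs, but by a formula that it does not show.

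**4. Dropout.**

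- Article: 22 + 2 = 24.
- Expected to remain after 10% loss: 24 × 0.9 = 21.6, which is 0.4 of a tooth below 22.
- Loss that 24 can absorb with 22 remaining: 2/24 = 8.3%.
- Enrolment that leaves 22 after 10% loss: 22/0.9 = 24.4, so 25 per group, 75 in total.

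**5. Power after the loss**, two-sided 1%. Ranges run over P1 = 0.999 with P2 = 0.533 and P1 = 0.9999 with P2 = 0.5333.

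| Per group | Pooled approximation | Printed (unpooled) formula | Fisher's exact test |
|---|---|---|---|
| 22 | 90.1–90.3% | 96.4–96.5% | 94.5–94.8% |
| 21.6 | 89.4–89.6% | 96.0–96.2% | not defined |
| 21 | 88.2–88.4% | 95.5–95.6% | 92.3–92.7% |

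Exact enumeration of the pooled z-test at 21 per group gives about 97%.

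**The case against.** The strongest reply is that 22 is a perfectly good sample size. The usual pooled formula reproduces it from the same inputs, so the defect lies in what was printed and not in how many teeth are planned. That stands.

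On dropout, multiplying by 1.1 instead of dividing by 0.9 is a common shortcut. Here it costs at most one tooth per group. Losing 2 of 24 leaves exactly 22; reaching 21 takes 3 losses, which is 12.5%. That stands too, and it is why this half of the point is minor.

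The two halves also do not add up to one larger error. If the printed formula governs, 18 is the requirement and 24 is ample even after dropout. If the pooled formula governs, 22 is right and the expected shortfall is under half a tooth.

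A reader might infer that the 90% power is lost once 10% drop out, pointing to 88% at 21 per group. The document's own figures do not support that. The 88% comes only from the pooled normal approximation, which is poor with a proportion this close to 1, and it rounds 21.6 down. The printed formula and the exact calculations all give more than 90% at 21.

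A reader might also infer that 22 must have come from the pooled formula. It is a plausible source, but the continuity-corrected version also rounds up to 22, and the article does not say which was used.

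None of this rescues the claim that 22 was obtained with the formula given.

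**Conclusion.** The stated result does not follow from the stated method. Formula (1) gives 17.0 to 17.1, which is 17 or 18 per group depending on which printed P1 and P2 are used, against 22 stated; the worked line gives about 8 when bracketed. This is an error of presentation in the sample size justification. It does not show that the trial is too small.

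The dropout allowance is short by 0.4 of a tooth per group on expectation, if 22 is the minimum. In other words, 24 per group covers about 8% loss, not 10%. Planned power is not materially changed.

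These conclusions take the article's assumptions as given: a two-group comparison of independent proportions, two-sided 1%, and satisfaction of about 100% against 53.33%. They say nothing on whether those assumptions are realistic.

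**What to change.** 1. Print the formula that was actually used to obtain 22, naming the variance form and any continuity correction. The authors must supply this; it should not be assumed to be the pooled version.
2. Correct the worked line to match that formula: outer brackets, squared difference in the denominator, and a single value of P1 throughout the section.
3. Keep 24 per group and restate the allowance in one of two ways. Either say that 24 allows for about 8% loss (2 of 24), or say that a 10% loss leaves 21 to 22 evaluable per group and give the power at that number for a named test. A bare figure of 88% should not be entered, because it belongs to one approximation only.

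This costs wording only and leaves the 72 teeth unchanged. If the authors prefer to keep a full 10% allowance above 22, the cost is one more tooth per group (25 each, 75 in total). The article states that the study has not yet started, so either correction can be made before enrolment.

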### Recruitment and consent

All the healthy children having more than one deciduous tooth decay requiring a crown will be selected for the study. Parents will be oriented on the implementation of the study.

The study protocol will be explained to the participating children and their parents. Further, a written informed consent will be obtained from their parents.

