### Study setting and population

The present study will be conducted in the Department of Pediatric and Preventive Dentistry of Sharad Pawar Dental College and Hospital, Sawangi (Meghe), Wardha, Maharashtra, India.

In children with more than one tooth requiring a crown, the teeth will be allocated based on random sampling. We will be conducting single blinding in which participants will be blinded. Personal information about potential and enrolled participants will be collected and maintained in order to protect confidentiality before, during, and after the trial. The population of the study is young, healthy children. The research is approved by the institutional ethics committee of Datta Meghe Institute of Higher Education and Research (Deemed to be University) (ref. no: DMIHER (DU)/IEC/2023/565). (IEC) Institutional Ethical Committee Date of approval: February 6, 2023.

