### Participant allocation/randomisation

The participants will be allocated based on the inclusion criteria. They will be randomized to preformed Bioflx crown and preformed zirconia crown as the intervention group or preformed stainless steel crown as the control group by computer-generated numbers. The research co-investigator will carry out data collection, data entry, and data analysis and will be blinded to group allocation.

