### Interventions

Total 72 primary teeth requiring crowns will be randomly distributed in three groups of 24 each. The allocation will be carried out using computer-generated numbers. After obtaining written informed consent, the subjects will be enrolled, and teeth will be assigned randomly to the groups for receiving the intervention or conventional preformed crowns.

Group 1: Preformed stainless steel crown: control group

(3M™ ESPE™)

The material for coronal build-up for this group is a preformed stainless-steel crown(the control group). An appropriate-sized preformed stainless-steel crown will be selected. Tooth preparation will be carried out with tapered bur (pyrax Dental Mani Diamond Burs TR-13C) to reduce occlusal surface up to 1 to 1.5 mm. The interproximal reduction will be made mesially and distally. The selected crown size will be checked and a trial fit will be done before cementation. It will require crimping pliers and the crown will be cemented using type 1 glass ionomer cement (GC Gold Label I/ Fuji I). The excess will be removed and proper occlusion will be checked.
^
8
^

Group 2: Preformed Bioflx crown

The Preformed Bioflx crown (
Kids-e-dental LLP [Limited Liability Partnership]) will be used in this group. A similar sized preformed crown will be selected. Tooth preparation will be carried out with a tapered diamond bur (pyrax Dental Mani Diamond Burs TR [Taper Round] -13C) for occlusal reduction by 1–1.5 mm, including the central groove. The proximal preparation will be around 0.5 mm to clear the contact area. Placement of the crown will be achieved by a snug fit followed by contouring using a How plier (GDC How Plier # Curved (3000/72).

Crown cementation will be carried out using a glass ionomer type I (GC Gold Label I/ Fuji I) and removal of excess cement using floss or explorer.

Group 3: Preformed zirconia crown

The material for crown restoration for this group is the preformed zirconia crown (Kids-e-dental LLP). A diamond bur will reduce the occlusal surface by 1.5–2 mm. Interproximally, contacts will be prepared with a tapered fissure bur. About 1–2 mm subgingival preparation will be performed. The selected crown will be placed and checked. The passive fit of the crown will be assessed and will be luted with dual cure resin cement (Prevest Fusion Ultra D/C / Dual Cure Resin). Consistent firm finger pressure will be applied during cementation. Crown placement will be assessed.
^
8
^

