### Data analysis and statistical plan

Statistical analysis will be done using general methodology; continuous variables will be summarized using tables of descriptive statistics: the number of patients with recorded observations, mean, standard deviation, median, minimum, and maximum. Categorical variables will be determined using counts and percentages. Descriptive statistics will be presented by diagnosis and all the results will be calculated using
RStudio Version: 2023.03.1+446 (RRID: SCR_000432) will be used. Comparison of continuous parameters between the three groups will be performed using an ANOVA test for quantitative data or Kruskal Wallis test for qualitative data. Categorical variables will be summarized using the frequencies and percentages and compared between the three groups.

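### The protocol contradicts itself on whether the tooth or the child is randomised and counted, so the 90% power for child satisfaction is not assured

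*Protocol article*

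**What the plan says.** The sections of the protocol article give different units.

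- **Tooth as unit.** Interventions states "Total 72 primary teeth requiring crowns will be randomly distributed in three groups of 24 each" and that "teeth will be assigned randomly to the groups for receiving the intervention or conventional preformed crowns". Study design says the same, and the Abstract also counts 72 teeth.
- **Several teeth in one child.** Study setting and population states "In children with more than one tooth requiring a crown, the teeth will be allocated based on random sampling". No section keeps a child to one study tooth or one crown type.
- **Child as unit.** Sample size opens with 72 teeth and closes "with a sample size of 72 children distributed in three groups". Participant allocation/randomisation says of the participants: "They will be randomized to preformed Bioflx crown and preformed zirconia crown as the intervention group or preformed stainless steel crown as the control group".
- **Who is recruited.** Recruitment and consent states "All the healthy children having more than one deciduous tooth decay requiring a crown will be selected for the study". The Eligibility criteria contain no multiple-tooth requirement, and the conditional wording in Study setting and population implies that some children have a single tooth.
- **Powered outcome.** Sample size relies on a cited study that "showed the difference between the two proportions of child satisfaction (%) as the primary variable", and uses a formula for two independent proportions.
- **Analysis.** "Comparison of continuous parameters between the three groups will be performed using an ANOVA test for quantitative data", with Kruskal-Wallis as the alternative.
- **Instruments.** Data collection describes satisfaction items on size, shape, color and stain, without saying whether they are scored per crown or per child. A separate parental scale rates impact on the child, for example smiling after crowns.

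**The concern.** The unit of randomisation fixes how many independent responses the trial has and what a response can be attributed to. If the tooth-based sections are followed and children bring several teeth, one child can receive crowns from two or three groups. A single answer about the child's smile or appearance then reflects all of those crowns, and no analysis can separate them afterwards. The number of children also falls to half of 72 or fewer, while the sample size assumes 22 independent children per group after dropout. Both consequences reach child satisfaction, the outcome on which the trial was sized. They are settled once the allocation list is drawn up, and Study status says the study has not begun.

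**Working it through.** **Inputs from Sample size:** P1 = 0.9999, P2 = 0.5333, two-sided alpha 0.01 (z = 2.576), power 90% (z = 1.28), 22 per group, 24 with dropout. **Assumptions, not in the documents:** the number of study teeth per child (m), the within-child correlation, and how a child with mixed crowns forms a rating.

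**1. The plan's own figure.** Pooled two-proportion formula, with mean proportion 0.7666:

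n = [2.576·√(2·0.7666·0.2334) + 1.28·√(0.9999·0.0001 + 0.5333·0.4667)]² / 0.4666² = (1.541 + 0.639)² / 0.2177 = 21.8, so 22.

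The stated 22 is reproduced. (The unpooled formula as printed gives 17; that is a separate matter.) Power at 22 independent children per group is 90% by normal approximation and 95% by Fisher's exact test. The losses below therefore do not come from the choice of test.

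**2. Children behind 72 teeth, and mixing.** With 72 teeth randomised 24:24:24, the chance that all m teeth of a child fall in one group is 3·C(24,m)/C(72,m). For m = 2 this is 23/71 = 0.324.

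| Teeth per child | Children | Share with more than one crown type |
|---|---|---|
| 2 | 36 | 67.6% |
| 3 | 24 | 89.8% |
| 4 | 18 | 96.9% |

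At m = 2 only about 36 × 0.324 = 11.7 children, or 3.9 per group, would carry a single crown type.

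**3. Power if each child keeps one crown type and gives one answer.** At m = 2, 36/3 = 12 children per group. Power at 1% is 30% (Fisher), 52% (z-test, exact calculation) or 56% (normal approximation). At m = 3, with 8 per group, it is 11% (Fisher) or 33% (normal approximation).

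**4. Power if teeth are randomised and a mixed child's probability of satisfaction is the average over its two crowns.** The second tooth is in the same group with probability 23/71 = 0.324 and in each other group with probability 24/71 = 0.338. Taking both esthetic crowns at P1 ≈ 1:

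- Experimental: 0.5 + 0.5·(0.324 + 0.338 + 0.338·0.533) = 0.921
- Control: 0.5·0.533 + 0.5·(0.324·0.533 + 0.676) = 0.691

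The gap shrinks from 46.7 to 23 points. Power with 22 per group is 17% (Fisher) or 27% (z-test). At m = 3 the rates are about 0.895 and 0.744, a gap of 15 points.

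**5. Type I error of the tooth-level ANOVA.** Simulation of 36 children with two teeth each, nominal 5%:

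| How a child's two teeth are allocated | Correlation 0.2 | Correlation 0.5 |
|---|---|---|
| Always the same group | about 8–9% | about 14% |
| Unconstrained | about 5% | about 5% |
| Always different groups | about 3–4% | about 2% |

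**The case against.** Three stronger conclusions are tempting, and the text supports none of them fully.

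*That children will certainly sit in several groups.* The closing sentence of Sample size, the participant wording in the allocation section and the Eligibility criteria leave room for 72 children with one study tooth each, and allocation by random sampling is loose wording. This stands. What can be shown is a contradiction and the consequences of one of its readings. The one-tooth reading would still have to be squared with Recruitment and consent, whose children have other teeth needing crowns of unstated type.

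*That satisfaction cannot be attributed to a crown at all.* Size, shape, color and stain are crown attributes and could be scored crown by crown. The text does not say that they are, nor that they are not. Only the impact scale is plainly about the whole child, and the trial was not sized on that scale.

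*That the planned ANOVA has the wrong error rate.* Under the unconstrained tooth randomisation that the text describes, it stays near 5%. Distortion needs a constraint that no section states. Naming a clustered model is also commonly left to the analysis plan, which is not shown, so its absence is not the point here.

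The power figures depend on the test and on the averaging rule, and the Fisher values are the low end. With 12 single-type children per group, or under the averaging rule, power is well below 90% by either test.

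**Conclusion.** The point holds as an internal contradiction with a material consequence, and it should be resolved before allocation begins. The sections disagree on whether teeth or children are randomised and counted, and on whether a child needs more than one affected tooth. Only the reading of 72 independent children matches the sample size calculation.

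Under the tooth-based reading with two teeth per child, 36 children supply the data and about 68% of them have mixed crowns. Power is about 30% to 56% with 12 single-type children per group, or about 17% to 27% with 22 per group under the averaging assumption. The contradiction follows from the text alone. The sizes rest on the assumed number of teeth per child and, for the second range, on the averaging rule. Attribution of the impact items fails for any mixed-crown child; attribution of child satisfaction fails unless it is rated per crown.

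**What to change.** Reconcile the Abstract, Study design, Study setting and population, Sample size, Recruitment and consent, Participant allocation/randomisation and Interventions to one unit.

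**Preferred:** randomise 72 children, the number Sample size already states, with one index tooth each for analysis. Change the recruitment sentence to at least one tooth needing a crown. Record the type of any other crowns in the child's mouth, because these can still color a whole-child rating; recording makes that influence visible but does not remove it.

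**If several teeth per child are kept:**
- state that satisfaction is rated per crown;
- analyse tooth-level outcomes with a random child effect or GEE clustered on child;
- do not enter a mixed-crown child's whole-child rating in more than one group;
- restate the power for the number of independent children.

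**Cost:** protocol wording, a revised randomisation list, and more children than a tooth-based count would need (72 rather than 36 at two teeth each). The clustered model costs only analysis time.
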